**Fig. 4 Fig4:**
[figure not shown]
Flow chart of the study

### Process evaluation

The second part of this research evaluates the process of implementation of the Blue Care ICA in the intervention neighbourhoods on macro (e.g. policymakers), meso (e.g. managers and directors) and micro (e.g. professionals and citizens) level. For understanding this process we use various methods of data collection, such as participant observation, analyzing meeting notes, semi-structured interviews, focus groups, and a citizen panel. We aim to capture the context in which Blue Care ICA will unfold and the thinking and practices that are tied to it. This allows for a more thorough understanding of both intervention delivery as well as aspects of the context in which the intervention is embedded. The Consolidated Framework for Implementation Research (CFIR) is used as an overarching framework to formulate a process evaluation plan. The CFIR model consists out of five major domains: intervention characteristics, outer setting, inner setting, characteristics of the individuals involved and the process of implementation [29, 37, 38]. These five domains comprise a total of 39 sub-domains. Table 3 shows an overview of the process evaluation questions, accompanying methods and timing of data collection. To conclude, the CFIR model provides a pragmatic structure for the complex, interacting, multi-level ICA in a ‘real world setting’ and works as an overarching, additional model for validated and frequently used implementation theories in public health, such as the innovation theory of Rogers [39] and the Re-Aim model [40]. Moreover, the CFIR model can be used for both summative and formative purposes, which is a major advantage for this research since sub-projects are developed over time and formative evaluation allows the researcher to give intermediate feedback to the implementers of the ICA. This contributes to the valorisation of this study.

**Table 3 Tab3:** Framework Process evaluation

Topic	Questions	Method/Source	Timing data collection
• Characteristics of the projects in the Blue Care ICA	- What are the characteristics of the projects developed ‘on the go’ in terms of the targeted audience and topic? And how do they contribute to the Quadruple Aim?	Observations, existing data sets, and semi-structured interviews with policymakers, health and social care professionals, citizens	T0, T1, T2, T3 (ongoing between 2017 and 2020)
• Citizen needs of the people living in the intervention neighbourhoods, • The influence of external policies on the Blue Care ICA	- Does the ICA meet the needs of the citizens and professionals living and working in the neighbourhoods? - Are there other contextual or environmental features which play a role in the experienced quality of life of citizens living in the neighborhood? - How do external strategies (policy and regulations / government) influence the pilot and the implementation?	Citizens: Citizen panel *n* = 10 × 2 (1 panel per two neighbourhoods) Policy: observations during existing board and financial sponsor meetings	Citizen Panel: T1, T2, T3 (meet 2 times a year) Policy: T0, T1, T2, T3 (ongoing between 2017 and 2020)
• Governance structure of the Blue Care ICA	- How is the governance model structured, how does this develop in these four years and what are the different roles in this structure (leadership, champions etc.)?	Observations during existing board and financial sponsor meetings, semi-structured interviews	T0, T1, T2, T3 (ongoing between 2017 and 2020)
• Implementation of the bottom up approach, • Collaboration, interaction and communication on macro, meso and micro level, • Use and implementation of Positive Health by health and social care professionals	- How are citizens and professionals actively involved and attracted in the pilot process (goal is bottom – up approach)? - How do healthcare and social service providers collaborate in the social domain at macro, meso and micro level and to what extent are they able to prioritize mutual interests above their own organisational interests? - How do professionals deliver person-centred care and support from a generalist perspective according to the principles of Positive Health, how do they implement Positive Health into their daily routine, and what is the influence on the type of care and support provided to citizens?	Participant observations at all levels, analyzing meeting notes, semi-structured interviews, focus groups with health and social care professionals, citizen panel	T0, T1, T2, T3 (ongoing between 2017 and 2020)

### Data analysis

Descriptive statistics will be computed to describe the characteristics of the target population in participating neighbourhoods (e.g., age, socioeconomic status, ethnicity, household composition) and to compare the intervention and comparison neighbourhoods at baseline. Relevant statistical tests (e.g., t-test, chi-square, analysis of variance, regression analysis) will be applied to analyse effects on the primary and secondary outcome measures (level of significance is 0.05; two-tailed). Data will be analysed according to the intention-to-treat principle. This means that all subjects included in the intervention group will be analysed as intervention subjects irrespective of whether they received the intervention or not. This allows for judging whether the neighbourhood population as a whole benefits from the Blue Care ICA, irrespective of whether citizens actually received (elements of) the intervention.

In all analyses, possible baseline differences between citizens from intervention and comparison neighbourhoods will be corrected for. In addition, subgroup analyses will be performed to investigate whether certain groups of citizens benefit more from the integrated community approach than others (i.e., according to age, gender, type of problems, socioeconomic status). Qualitative data will be analysed using narrative descriptions of procedures and meetings, identifying themes in the focus group with professionals, citizens’ panels, and semi-structured interviews with citizens, professionals, managers, and directors. Interviews will be transcribed verbatim and Nvivo 12.0 will be used for the analysis.

Descriptive statistics will be used to describe the total amount of reimbursement at the population level over time as well as (changes in) the proportion of reimbursement in the social domain (on account of the Social Support Act, the Youth Act and the Participation Act) and in the health care domain (on account of the Health Insurance Act, e.g., primary care, hospital care, mental health care, medication and diagnostics).

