#### Combining budgets

The third core element, ‘combining budgets’, will build a reimbursement system in which the budgets for health and social care are combined on a population level. Therefore, the budgets of the dominant health insurer in the south of Limburg (VGZ, Health Insurance Act) will be combined with the budgets of the social care domain (Social Support Act, Youth Act and Participation Act).

The financial reimbursement system is agreed upon at the macro (policy) level and is considered to be a prerequisite for enabling and facilitating the implementation of initiatives at the micro and meso (community and organizational) level. The national budgets of the Long –Term Care Act will not be included in the budget of the Blue Care ICA, even though the costs in this area will be monitored along the way. The objective is that the costs of health and social care, following the implementation of projects within the Blue Care ICA, will be in accordance with available financial budgets (thereby breaking the trend of increasing costs) or, ideally, that projects will lead to a decrease in costs. To judge this, the reimbursements of 2015 in these domains will be used as an upper limit.

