## Methods/ study design

### Study design

Overall, a mixed-methods approach, combining both quantitative and qualitative research methods, is applied to yield an enriched understanding of the various processes that will take place in the neighbourhoods aiming to improve population health, the perceived quality of care, work satisfaction of professionals and to reduce per capita costs. The Blue Care ICA is being implemented in the four intervention neighbourhoods between 2017 and 2020, and research activities will be conducted parallel to the implementation process. The research focusses on two parts: (1) the effects of the Blue Care ICA on Quadruple Aim outcomes and (2) the implementation process of the Blue Care ICA in the four neighbourhoods of Maastricht.

Our investigation of the effectiveness on population health and (experienced) quality of care of the program utilizes a prospective, quasi-experimental design. The study can best be considered a ‘natural experiment’ [28], as the research will follow the natural course of the development of the Blue Care ICA in daily practice. It aims to test whether it is likely to be effective in routine practice by comparing it to neighbourhoods where this approach is not implemented (comparison neighbourhoods).

To measure its effects on work satisfaction of professionals and per capita costs, both qualitative and quantitative methods will be used. To determine how the Blue Care ICA is embedded in the four neighbourhoods, a process evaluation plan is designed using the Consolidated Framework for Implementation Research (CFIR) as an overarching framework [29]. An overview of the study design including a global overview of data collection measures and timing of data collection is provided in Fig. 3.

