#### Costs

To investigate the influence of the Blue Care ICA on per capita costs, two levels for computing reimbursements retrospectively are distinguished: population level and user level. First, the amount and the trend in the annual reimbursements during the intervention period (T0-T3) in the health and social care domain (care and support financed under the Health Insurance Act by the health insurance company and the Social Support Act/Youth Act/Participation Act/Public Health Act by municipalities) are computed on a population level for the citizens in the four neighbourhoods where the Blue Care ICA is being implemented (total amount as well as mean per citizen). These reimbursements will be compared to the reimbursements in the reference period 2015–2016 and to the comparison neighbourhoods (risk –adjusted standardized reimbursements) as well as the national figures to investigate whether a break in the trend of increasing costs will appear at the population level. Furthermore, the annual mean volumes of used medical services and services in the social care domain will be computed for both the intervention and comparison neighbourhoods to investigate whether changes in the number of used services took place (user level).

Health care costs with data related to health and social care, as well as reimbursement data will be collected via existing databases and registration systems from the health insurer VGZ, the municipality of Maastricht, and Statistics Netherlands (CBS, national statistics database with an overview of volumes and costs of both health as social care).

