### Sample size considerations effect measure

The sample size calculation for the study is based on the primary outcome measure health-related quality of life, measured with the SF-12v2. To demonstrate a clinically relevant treatment difference of 3.0 on the Mental Component Summary Scale Score, given SD = 8.88 [36], and an alpha of 0.05 and a power of 0.80, the minimally required number of participants is 138 per study. In order to demonstrate the effects of the ICA on the subpopulation level with respect to age (18–65 years vs. 65 years and older), 138 participants per age category are required, resulting in a total of 2 × 138 = 276 participants per study group. The total required sample size (intervention + comparison group) is therefore 552 (2 × 276).

It is expected that 15% of all citizens approached for participation by means of an information letter and consent form will agree to participate. Additionally, a drop-out rate of 50% between T0 and T3 is expected. Accounting for drop-out, 1104 citizens need to be enrolled at T0 (552 per study group). Based on the expected response rate of 15% across all age groups and neighbourhoods, 7360 citizens (3680 per study group) need to be approached for participation. As the required number of participants to be approached per study group closely resembled the number of clients in the general practice population that were eligible for inclusion (at least for the comparison group), we decided to approach all eligible citizens to prevent selection bias. Figure 4 presents a flow chart of the study based on the actual number of citizens approached for participation, the expected response rate and the expected drop-out rate.

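### The study sets out to measure an effect on per capita costs, but the only analysis named for reimbursements is descriptive, with no measure of uncertainty on the controlled contrast

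*Protocol article*

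**What the plan says.** The Study design section treats cost as something on which an effect is measured: "To measure its effects on work satisfaction of professionals and per capita costs, both qualitative and quantitative methods will be used". The Costs section gives the purpose, "to investigate whether a break in the trend of increasing costs will appear at the population level", and the references: "These reimbursements will be compared to the reimbursements in the reference period 2015–2016 and to the comparison neighbourhoods (risk –adjusted standardized reimbursements", followed by national figures. The Combining budgets section adds a budget criterion: "To judge this, the reimbursements of 2015 in these domains will be used as an upper limit".

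The Data analysis section then names the method for reimbursements: "Descriptive statistics will be used to describe the total amount of reimbursement at the population level over time", together with the shares spent in the social and health care domains. The tests in that section "will be applied to analyse effects on the primary and secondary outcome measures (level of significance is 0.05; two-tailed". Table 2 lists those outcome measures: SF-12v2, EQ-5D-5L, Resilience Scale, Spiderweb and quality of care. Reimbursements are not among them. The same section also states: "In all analyses, possible baseline differences between citizens from intervention and comparison neighbourhoods will be corrected for".

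**The concern.** Lower per capita cost is one of the four Quadruple Aim goals, and the Discussion repeats that effects on those goals will be measured. An effect on cost is a causal statement: spending differed from what it would have been without the programme. Even a complete count of residents does not settle that, because who falls seriously ill, and so who incurs very high costs, varies by chance from year to year.

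A descriptive table of totals and means carries no indication of how large that variation is. Readers of the main outcome report could take a modest gap from the comparison neighbourhoods as a programme effect. A real effect of similar size could equally be dismissed. The article does not leave the cost method open. It names one, and that method does not answer the effect question.

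**Working it through.** **The plan's own figure.** The only powered calculation is for the SF-12v2: "clinically relevant treatment difference of 3.0 on the Mental Component Summary Scale Score, given SD = 8.88", with alpha 0.05 and power 0.80. It reproduces: 2 × (1.960 + 0.842)² × 8.88² / 3.0² = 137.5, rounded up to 138, and 2 × 138 = 276 per study group. It does not concern costs, for which no precision is stated.

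**Inputs from Table 1.**
- Intervention residents: 3,280 + 2,370 + 4,015 + 5,706 = 15,371.
- Comparison residents: 4,965 + 2,415 + 3,410 + 5,345 = 16,135.

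**Assumptions, not in the document.**
- The coefficient of variation (CV) of annual cost between persons is 2–4.
- The within-person correlation between years (ρ) is 0.3–0.7.
- Both areas are closed populations of independent persons, with no shocks specific to a neighbourhood.
- Variances are not reduced for risk adjustment.

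**Formula.** For the difference between areas in the relative change from one year to another:

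SE = CV × √(2(1 − ρ)) × √(1/15,371 + 1/16,135), where the last factor is 0.01127. The 95% half-width is 1.96 × SE.

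**Results.**
- CV 2, ρ 0.7: 1.96 × 2 × 0.775 × 0.01127 = 3.4%.
- CV 3, ρ 0.5: 1.96 × 3 × 1.000 × 0.01127 = 6.6%.
- CV 4, ρ 0.3: 1.96 × 4 × 1.183 × 0.01127 = 10.5%.

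**What chance alone would show.** With no true effect, the probability that cost growth looks at least 2 percentage points slower in the intervention area is Φ(−0.02/SE). In the same three cases it is 0.13, 0.28 and 0.35.

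**Scale of a plausible effect.** Suppose, for illustration, that growth is halved from 2% to 1% a year for three years. The level then changes by (1.02³ − 1.01³)/1.02³ = 2.9%, which is below even the smallest half-width above.

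**Sensitivity.**
- The plan has two reference years. Setting one later year against the mean of 2015 and 2016, with equal correlation between all years, multiplies the half-width by √((1 + 1/2)/2) = 0.87. The range becomes about 3.0–9.1%.
- If usable data covered only half the residents (assumed), the half-widths would be √2 = 1.4 times larger.
- Any variation specific to a neighbourhood adds to all these figures.

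**The case against.** Several arguments on the other side have force.

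- **A controlled contrast is already planned.** The Costs section provides for risk adjustment, comparison neighbourhoods and national figures, and baseline differences are to be corrected for. This stands. A reader might infer an uncontrolled before-after reading, and the document does not support that. But these steps deal with shared trends and case mix; they do not show how much of the remaining difference is chance.
- **No rule treats a one-year dip as success.** This also stands. A reader might infer that any single-year fall would be reported as a programme effect, but no section says so. The concern rests on the contrast between areas, not on falls within the intervention area.
- **The 2015 ceiling is accounting.** Whether money paid stayed within a budget needs no interval, so descriptive totals suffice for that question.
- **The wording is mixed.** The research questions ask for effects on quality of life and quality of care, but only for changes in reimbursements, and costs are not a listed outcome. Description would fit that reading. The Study design, Costs and Discussion sections nevertheless speak of effects or influence on cost, so the tension is in the document itself.
- **An article leaves details to a fuller plan.** That would excuse silence on the method. Here a method is stated, in contrast to the tests named for the other outcomes.
- **The variances are assumed.** True. The half-widths depend on them, and risk adjustment may narrow them.

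**Conclusion.** The point holds in a limited form. The protocol sets out to measure an effect on per capita costs through a reasonable controlled comparison, but the one analysis it names for reimbursements gives no measure of uncertainty on that comparison. Under the assumed CV of 2–4 and year-to-year correlation of 0.3–0.7, the 95% half-width is about 3.4–10.5% before any variation between areas. A difference of a few per cent therefore cannot be attributed to the programme, or ruled out, from descriptive figures alone.

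The exact range rests on inputs that the document does not give. That a descriptive summary cannot separate effect from chance does not depend on them. The finding does not touch the budget check against 2015 or the primary outcome.

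**What to change.** Keep the descriptive tables, and keep the comparison with the 2015 ceiling, labelled as accounting.

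For the effect question, add the difference-in-differences in risk-adjusted mean annual reimbursement per citizen: the change from 2015–2016, intervention minus comparison neighbourhoods. Give it a 95% confidence interval that reflects variation between neighbourhoods and years as well as between persons. Resampling persons alone would give too narrow an interval, because there are only four neighbourhoods per group. Show the eight neighbourhood series alongside. Attribute a break in trend to the programme only as far as the interval supports it, and avoid a pass/fail significance rule.

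If the necessary variances cannot be obtained from the insurer, municipal and national sources, state that the cost results are descriptive and support no effect claim.

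The cost is modest extra analysis on data sources already named. The interval will probably be wide and inconclusive: if each neighbourhood contributes one change, it rests on 8 − 2 = 6 degrees of freedom.

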### Registration, ethics and data management

The study is registered with the Dutch Clinical Trial Registry (NTR) (https://www.trialregister.nl/trial/6359 NTR6543; registration date July 25th, 2017).The current study protocol (version 1) is the version for which The Medical Ethical Committee (METC) of the Maastricht University Medical Center (MUMC+) waived the need for ethics approval. Data will be collected between 2017 and 2020. Any amendments to the original protocol will be announced to the METC and the NTR. The research team located at the Department of Health Services Research at Maastricht University will be responsible for the data management and this will be in accordance with the data – management protocol of Maastricht University. Confidential data is stored in a secure place, separated from personal response datasets. The main researcher and a trained research assistant will be the only persons who have access to the personal confidential data. The primary funder of this study is The Netherlands Organisation for Health Research and Development (ZonMw). ZonMw has no role in the intervention, research nor the publication of the data. Data retention and possible dropouts will be minimised by a postal reminder when there is no initial response from the participants. Collected and analysed data on a group level, which is not traceable to individuals, will be shared in a ‘main outcome report’ with the citizens, professionals and other stakeholders of the Blue Care ICA.

## Discussion

In this paper, the design of a mixed-methods study, including a prospective, quasi-experimental study and a thorough process evaluation, is presented. It aims to measure the effects of the Blue Care ICA on Quadruple Aim outcomes and to investigate the implementation process of Blue Care ICA in four low socioeconomic neighbourhoods of Maastricht.

The Blue Care ICA, as described here, poses challenges for the design of an evaluation study to investigate effects and the implementation process. First, exposure to the Blue Care ICA at the individual level cannot be manipulated (i.e., randomised) by a researcher, as it would restrict obtaining an objective and real-life picture of the distribution of budgets, delivery of care or services in the health and social care domain, and the development of initiatives by citizens. Experimental manipulation at the neighbourhood level is also not feasible, as these neighbourhoods and the organizations involved have signed an intention to implement the Blue Care ICA, based on the ideology of Positive Health and by combining budgets. Furthermore, instead of a fixed intervention with clear guidelines for implementation, variability in content and implementation can be expected, as the projects of the Blue Care ICA need to evolve over time and require translation into daily working routines during the process of implementation. Additionally, implementation of the intervention can be challenged by external and internal factors (e.g., political elections or re-organisations of the organizations important stakeholders participate in). Correspondingly, we do not know beforehand which specific sub-projects will be developed, since the Blue Care ICA is a bottom-up approach, trying to fill in the gaps where the existing social and healthcare system fails in these four neighbourhoods. The projects are developed to address the Quadruple Aim goals and are also created based on the needs of citizens and professionals instead of implementing a fixed theory or intervention protocol. This makes it challenging to determine beforehand which activities can be an object of research. Nevertheless, the chosen research design presented in this article provide a thorough research direction and guidance that also allows enough room for the researcher to incorporate the research needs of the sub-projects which are developed ‘on the go’. The process evaluation will provide insight into the extent to which these factors contributed to the outcome and effects of the intervention. Results of the effect and process evaluation will become available in 2020.

